**Fig 2 Fig2:**
[figure not shown]
Definition of primary endpoint UTI for ProSCIUTTU (need to refer to Table 2)

**Table 2 Tab2:** Definition of "symptomatic UTI" as primary endpoint for ProSCIUTTU (need to refer to Fig. 2). Use the following table to assess “Category 1”, or Two “Category 2” and any “Category 3” Symptoms: All symptoms should be asked in each category

“*Category 1*” *Symptoms:**	“Category 2” Symptoms:*	“Category 3” Symptoms:
	Two or more	In themselves not enough to lead to treatment but recorded for International Spinal Cord Injury Urinary Tract Infection Datasets Compatibility
• Temperature: Greater than 38 ° C core Greater than 37.5 ° C per axilla • New or increasing symptoms of Autonomic Dysreflexia, as detected by any of the following signs: *Pulse < 50 or increased flushing or sweating or headache AND increased B.P Diastolic or Systolic > 25 % usual baseline.*	• Increased Frequency of Muscle Spasms or spasticity • Failure of usual control of urinary incontinence- *any of the following constitutes fulfillment of this category* -Bladder Spasm -Urinary frequency or need for increased catheterization -Urinary Retention -Urinary Urgency -Leaking around catheter site or per urethra if have suprapubic catheter • New Scrotal/Loin/Abdominal Discomfort unexplained by other pathology - *any of the following constitutes fulfillment of this category* -Abdominal Pain -Bladder/Suprapubic Pain -Loin/Back Pain -Scrotal Pain -Dysuria	*any of the following constitutes fulfillment of this category* -Anxiety/uneasiness -Feeling tired -Feeling sick -Arthralgias/Body Aches -Chills -Diaphoresis/sweating -Cloudy Urine -Foul smelling urine -Blood in urine *haematuria* -Catheter blockage

*Content adapted and modified from Box 1 of Spinal-injured neuropathic bladder antisepsis (SINBA) trial [4]The secondary endpoint is time to change of MRO colonisation status as determined by two successive cultures [See guidelines for MRO change or clearance in Additional file 1].

### Data analysis

All analyses of outcomes will be by intention to treat, apart from safety outcomes which will be according to actual treatment received. Primary and MRO outcomes will be analysed using survival analysis. Cox regression modelling will be performed to test the effect of each treatment while allowing for the other, assuming no interaction effect. Hazard ratios and Kaplan-Meier survival curves will be used to summarise results. The extremely high prevalence of MRO in SCI will also allow us to explore whether probiotics can treat [or prevent] MRO colonisation in this group.

A survey was sent out to selected co-authors for determining the strength of association of several variables in regards to UTI in the SCI population [pre hoc review]. Only variables which have strong or moderate association will be included in the analysis.

Biofilms will be analysed using a combination of RNA based meta-community sequencing, TRFLP fingerprinting and culture based methods.

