**Fig 1 Fig1:**
[figure not shown]
Participant Study Flow Chart for ProSCIUTTU

Active Interventions:GR1-RC14. Concentration per capsule is 5.4 × 10^9^ colony forming units.LGG-BB12. Concentration per capsule is 7 × 10^9^ colony forming units.

Participants will be assessed at Day 0, 3 months and 6 months, supported by fortnightly phone calls to determine health status and confirm intercurrent symptomatic UTI status. [Fig. 1] Following witnessed informed consent, evaluations conducted will be:Intervention issues and compliance.Quality of life assessment with the Short Form Health Survey [SF-36] – baseline and 6 months plus study endpoint if reached.Microbiological swabs of rectum, nose and groin, urine culture and collection of urinary catheters for participants with indwelling or suprapubic catheters – baseline, 3 months and 6 months. Urine cultures also performed if at study endpoint. Specific instructions for sampling were given by study co-ordinator to research assistants and community nurses performing the swabs to ensure consistency.Bowel questionnaire [13, 14] - baseline and 3 months.

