### Feasability, safety, efficacy

#### Efficacy

The primary study endpoint is symptomatic UTI with microbiological evidence of infection [refer to Fig. 2 and Table 2]. However, other secondary measures of interest include:Clinical infection.Hospital admissions and intensive care unit admissions related to infection.A diagnosis of laboratory infection defined by a positive blood culture.Clinical adverse events [grade 3–4] regardless of causality.All causes of mortality.Use of antibiotics.Change in of MRO colonisation/infection status as defined by two consecutive MRO swabs three months apart.Modifications of bladder management.SF-36A cost-effectiveness analysis will be undertaken using SF-6D utility weights derived from the SF-36. In addition to antibiotic use, the following resource data will also be collected during the study:Use of isolation precautions: Single room; Personal Protective Equipment [PPE];Isolation ward;Terminal cleanInfection control auditing

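### The MRO outcome is assigned to Cox and Kaplan-Meier analysis, although the swab schedule gives only one or two event times and the true time of change is interval-censored

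*Protocol article*

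**What the plan says.** Four places in the Protocol article bear on this outcome.

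- **Data analysis** names the method: "Primary and MRO outcomes will be analysed using survival analysis". It specifies Cox regression with both treatments in the model, and adds: "Hazard ratios and Kaplan-Meier survival curves will be used to summarise results".
- **Study endpoints**, in the note under Table 2, defines the outcome: "The secondary endpoint is time to change of MRO colonisation status as determined by two successive cultures". It refers to Additional file 1 for the rules on change or clearance.
- **Efficacy** gives the spacing: "Change in of MRO colonisation/infection status as defined by two consecutive MRO swabs three months apart".
- **Participants**, in the list of evaluations after Fig. 1, sets the schedule. The item opens "Microbiological swabs of rectum, nose and groin, urine culture and collection of urinary catheters" and ends "suprapubic catheters – baseline, 3 months and 6 months". The only unscheduled sample is a urine specimen: "Urine cultures also performed if at study endpoint".

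The MRO paragraph under Sample size is framed in proportions: about 40% positive at enrolment, 5-10% of controls becoming negative, and a 15-20% difference detectable with 372 participants.

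**The concern.** Cox regression and Kaplan-Meier curves draw on the order in which events occur. The urinary infection outcome provides that order, because symptom onset is dated and participants are telephoned every fortnight. The MRO outcome does not. Status is seen at three visits, so a change is known only to lie between two of them, and almost every event is tied with the others. The plan applies the same continuous-time method to both outcomes.

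At stake is the size and meaning of the reported effect. A figure labelled a hazard ratio could be a risk ratio, a grouped-time hazard ratio or close to an odds ratio, depending on a software setting. The Kaplan-Meier curve would have one or two steps if drawn on visit times. If drawn on collection dates, its shape would reflect when swabs were booked.

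**Working it through.** **1. Number of possible event times.** Swabs are scheduled at months 0, 3 and 6, and a change needs two successive results three months apart.

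- If both confirming swabs must come after baseline, the only usable pair is months 3 and 6. There is one event time, and a change first seen at month 6 cannot be confirmed.
- If baseline may be the first of the two, the pairs are 0-3 and 3-6. There are two event times.

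**2. The plan's own MRO figure.** Inputs from Sample size: 40% of 372 = 148.8 MRO-positive, or 74.4 per factorial margin. I read the 15-20% as percentage points of extra clearance. For 5% against 20% (two-sided 5%, 80% power, pooled variance under the null, no continuity correction):

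n = [1.96 × √(2 × 0.125 × 0.875) + 0.842 × √(0.05 × 0.95 + 0.20 × 0.80)]² / 0.15² = 75.1, so 76 per margin.

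That is 152 positives, or 152 / 0.40 = 380 in total against the stated 372. Power at 74 per margin is 79.4% for 5% v 20%, 93.4% for 5% v 25%, 86.8% for 10% v 30% and 67.4% for 10% v 25%. Apart from the last pair, the figure reproduces, within rounding, as a comparison of two proportions.

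**3. What Cox returns with one event time.** Take 75 per margin (74.4 rounded up), with 4/75 changed in control and 15/75 on treatment. Each fit compares two groups, without the other factor or the strata.

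- Breslow: the partial likelihood is maximised at the risk ratio, (15/75)/(4/75) = 3.75. Its SE on the log scale is √(1/4 + 1/15) = 0.563. The usual SE of a log risk ratio is √(1/4 − 1/75 + 1/15 − 1/75) = 0.539, so Breslow is about 4% too wide.
- Efron: 4.05, SE 0.563. The complementary log-log hazard ratio is ln(1 − 15/75)/ln(1 − 4/75) = 4.07, SE 0.563.
- Exact-discrete: approximately the odds ratio, (15 × 71)/(60 × 4) = 4.44.

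For 8/75 v 22/75 the values are 2.75 (Breslow), 3.06 (Efron; complementary log-log 3.08) and 3.48 (odds ratio). Breslow and Efron both have SE 0.413.

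**4. Across the planned rates, one time against two.** Fitted hazard ratios at 74 per margin. For two times, events are split about equally between the visits.

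| Control v treated | Event times | Breslow | Efron | Exact-discrete | Highest over lowest |
|---|---|---|---|---|---|
| 5% v 20% | one | 3.75 | 4.05 | 4.41 | 18% |
| 10% v 25% | one | 2.57 | 2.79 | 3.05 | 19% |
| 10% v 30% | one | 3.14 | 3.52 | 4.01 | 28% |
| 5% v 25% | one | 4.50 | 4.98 | 5.56 | 24% |
| 5% v 20% | two | 3.90 | 4.05 | 4.21 | 8% |
| 10% v 25% | two | 2.69 | 2.80 | 2.93 | 9% |
| 10% v 30% | two | 3.35 | 3.54 | 3.77 | 13% |
| 5% v 25% | two | 4.74 | 4.98 | 5.24 | 11% |

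The gap between Breslow and Efron alone is 8-12% with one time and 4-6% with two. Every fit has p below 0.05. The largest is 0.034 (Breslow, 10% v 25%, one time), against 0.020 for exact-discrete in the same case.

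**5. Actual dates in place of nominal visits.** If swab dates are assumed to vary by ±14 days, the median Breslow-Efron gap for the two one-time examples in step 3 falls to 0.6% and 0.9%. The ties are then mostly broken, but by the calendar of visits.

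**The case against.** The best defence has several parts.

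- **Additional file 1 holds the rule and is not shown.** This stands. A reader might infer from the swab spacing that exactly one event time is possible, but the documents do not settle that. Study endpoints speaks of cultures, and a urine culture taken at a urinary infection might supply an extra date for some participants. The swab-based definition under Efficacy points against that without excluding it.
- **Real dates remove the ties.** Largely true, as step 5 shows. The interval-censoring remains, and the order of events then carries no information about colonisation.
- **A hazard ratio can still be estimated.** True. A reader might conclude that the stated effect measure does not exist in these data. It does: the complementary log-log model estimates a grouped-time hazard ratio, and Cox with Efron ties nearly reproduces it (4.05 v 4.07; 3.06 v 3.08).
- **The tie option does not set the precision.** Also true: Breslow and Efron have equal SEs in both worked examples. The odds-ratio SE differs mainly because the scale differs.
- **Sizing on proportions and analysing times is ordinary practice.** Accepted. The primary outcome is sized the same way, so the sizing paragraph is not itself an error. It only shows that a binary analysis would fit the planning.
- **Tie handling belongs in the statistical analysis plan.** Its absence here is no finding. The article does, however, name a continuous-time method for this outcome and fix a sampling schedule that does not suit it.

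**Conclusion.** The point holds as a mismatch between a stated method and the data that the schedule can produce. There are one or two scheduled event times, and the true time of change is interval-censored. On nominal visit times, the choice of tie method moves the reported hazard ratio by 18-28% from lowest to highest with one event time and by 8-13% with two. Part of that spread reflects three different effect measures under one label. On actual dates the numerical spread mostly disappears, but the ordering is by appointment.

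These sizes rest on the planning rates under Sample size, about 74-75 MRO-positive participants per margin, complete swabs, and two-group fits without strata. Significance did not change in any planned scenario and the endpoint is secondary. The consequence is therefore an ambiguous effect size and an uninformative curve, and no conclusion about efficacy is shown to be wrong. The change is worth making because it is cheap.

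**What to change.** Under Data analysis, restrict Cox regression and Kaplan-Meier curves to the urinary infection outcome. For the MRO outcome:

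1. State which pairs of results can establish a change and what date it is given, consistent with Additional file 1.
2. Analyse MRO change by 6 months as a binary outcome, separately for participants positive at baseline (clearance) and negative at baseline (acquisition). Use a regression with both treatment factors and the randomisation strata (bladder management and inpatient status). Report a risk difference or risk ratio with a 95% confidence interval.
3. If the rule allows change at both 3 and 6 months, use a two-interval complementary log-log (grouped proportional hazards) model instead. This keeps a hazard ratio with a clear meaning.
4. State how participants missing the 3- or 6-month swab are handled, for example by multiple imputation.

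The cost is a change of wording, with no new data. The main downside is the missing-swab rule in item 4: a definition needing both post-baseline swabs loses anyone who misses either one.

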### Sample size

The trial uses a factorial design which allows the two probiotics to be compared with placebo simultaneously without inflating the sample size, on the assumption that they do not interact with each other. [Refer Table 1].

**Table 1 Tab1:** Study design for ProSCIUTTU

	LGG -BB12 (B) Active (186)	LGG -BB12 (b) Placebo (186)
GR1-RC14 (A) Active (186)	AB or Intervention A (93)	Ab or Intervention B (93)
GR1-RC14 (a) Placebo (186)	aB or Intervention C (93)	ab or Intervention D (93)

UTI prevention: In our previous RCT with the same study population [4], 45 % of participants had a symptomatic UTI within six months. To have 80 % power to detect [at 5 % two-sided significance level] a 30 % reduction in the treatment group requires a total sample size of 350. Allowing for a 5 % loss to follow-up a final sample size of 372 is required, 93 participants being randomly allocated to each of the four study groups.

MRO treatment: It is expected that approximately 40 % participants will be MRO-positive at enrolment. Assuming 5-10 % become MRO-negative in the control group, a 15–20 % reduction in MRO-positive colonisation rate with probiotics would be detectable as significant at the 5 % level, with 80 % power, with a sample size of 372.

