### Randomisation and blinding of assessors

A simple stratified [computer generated] randomisation protocol is used. JS is responsible for generating the allocation sequence. Randomisation is stratified by bladder management types [indwelling/suprapubic vs intermittent catheters vs condom drainage/reflex voiding] as well as inpatient/outpatient status. Randomisation occurs following participant’s compliance check at Day 4. One central pharmacy is responsible for the assignment and distribution of the intervention for the entire study. All four treatment regimens will be indistinguishable by appearance and taste, and all participants receive the same quantity of tablets. All clinical staff, researchers and participants remain blind to treatment allocation throughout this process. An audit of randomisation, product allocation and dispensing stock will be performed at the completion of the study by MT, who is not affiliated with the final analysis and the clinical management of the study or study participants.

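### The covariate rule for the Cox model does not guarantee that the randomisation strata enter the primary analysis

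*Protocol article*

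**What the plan says.** The protocol article, under Randomisation and blinding of assessors, states: "Randomisation is stratified by bladder management types [indwelling/suprapubic vs intermittent catheters vs condom drainage/reflex voiding] as well as inpatient/outpatient status". Three bladder categories by two settings make six strata. The scheme itself is described in one line: "A simple stratified [computer generated] randomisation protocol is used".

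Under Data analysis, the primary model is given as: "Cox regression modelling will be performed to test the effect of each treatment while allowing for the other, assuming no interaction effect". The Method part of the abstract describes the same model. Neither place mentions the stratification factors.

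The covariates come from a different source: "A survey was sent out to selected co-authors for determining the strength of association of several variables in regards to UTI in the SCI population". The article labels this a pre hoc review. The rule that follows is: "Only variables which have strong or moderate association will be included in the analysis". The variables surveyed and the ratings they received are not listed.

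**The concern.** Factors used to stratify randomisation normally belong in the primary model because the design used them. Here the only stated route into the model is a rating of strong or moderate in a survey. Read as written, a stratification factor enters only if it was put to the co-authors and they rated it highly. One factor could be kept and the other dropped.

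This is more than a detail left to a statistical analysis plan. The article states an inclusion rule, and the rule has no exception for the design factors.

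The stake is efficiency, not validity. In a Cox model, leaving out a prognostic factor moves the treatment hazard ratio towards 1 relative to its within-stratum value and lowers power. Balance achieved by stratifying does not prevent this. If chance imbalance within strata did occur, adjustment would also correct for it. There is little power to spare: Trial status reports 207 participants recruited, against 372 planned.

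**Working it through.** **Inputs from the protocol article (Sample size, Trial status).** The control risk rests on an earlier trial in which "45 % of participants had a symptomatic UTI within six months". The target is a 30 % reduction, with a two-sided 5 % test and 80 % power. The stated totals are 350 before and 372 after loss to follow-up, and 207 were recruited.

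**Implied effect.** Treated risk = 0.45 × 0.70 = 0.315. With proportional hazards, HR = ln(1 − 0.315) / ln(1 − 0.45) = ln 0.685 / ln 0.55 = 0.633. Average risk = (0.45 + 0.315) / 2 = 0.3825.

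**The plan's own figure.** It is not reproduced from its two-sided inputs:
- Two proportions, no continuity correction: 406 in total.
- Schoenfeld: 150 events, 150 / 0.3825 = 392.
- Freedman: 156 events, 156 / 0.3825 = 408.

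Power at 350 is 74.0 % by proportions and 75.4 % by Schoenfeld. At 207, about 207 × 0.3825 = 79 events are expected, and Schoenfeld power is about 53 %. The sample size is a separate matter. It is shown here because it sets the baseline of about 74–75 % against which the table below should be read.

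**Assumptions that the article does not supply.** Bladder types in shares 40/40/20; 20 % inpatients. For a stratum hazard ratio *h*, one bladder type (40 %) has *h* times the hazard of the other two, and inpatients have *h* times the hazard of outpatients. The baseline hazard is set so that the control risk averages 45 %. The tested treatment is balanced within strata, its true within-stratum HR is 0.633, the other treatment has no effect, and there is no loss to follow-up. N = 350, 1,500 simulated trials per scenario.

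**Models compared, each containing both treatments.** (a) No strata; (b) Cox model stratified by the six strata; (c) strata factors as covariates.

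| Stratum HR *h* | HR (a) / (b) / (c) | Power %, (a) / (b) / (c) | Gain in points, (b) − (a) / (c) − (a) |
|---|---|---|---|
| 1 (not prognostic) | 0.634 / 0.634 / 0.632 | 73.7 / 73.2 / 73.8 | −0.5 / +0.1 |
| 1.5 | 0.634 / 0.630 / 0.629 | 73.5 / 73.9 / 74.9 | +0.4 / +1.4 |
| 2 | 0.640 / 0.628 / 0.627 | 71.6 / 73.7 / 74.9 | +2.1 / +3.3 |
| 3 | 0.667 / 0.635 / 0.633 | 65.7 / 73.7 / 74.7 | +8.0 / +9.0 |

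Monte Carlo error on each power is about 1 point. The half-point loss in the first row is within that error.

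**Sparse cells.** With the same assumed shares, the smallest stratum at 207 participants would hold 207 × 0.20 × 0.20 ≈ 8 people and about 8.3 × 0.3825 ≈ 3 events, spread over four arms. This is why a collapsing rule is needed.

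**The case against.** The strongest reply is that the harm largely cancels itself. Attenuation and power loss need strongly prognostic strata, and the survey rule is meant to keep variables of that kind. If the strata are weak, leaving them out costs almost nothing. The simulation also compares a model with no covariates against one with the strata, whereas the plan would include whatever the survey retained. The table therefore shows the loss when both factors are dropped and nothing related replaces them.

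Much of this stands, and it limits the size of the point. It does not remove it. The rule acts on the opinion of selected co-authors, not on measured prognostic strength, and nothing shows that both factors were surveyed.

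A second reply is that the restriction may be meant only to filter the surveyed candidates, with the design factors handled in the analysis plan. That reading is possible, but the sentence does not say so.

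A reader might also infer three stronger things that the document does not support:
- **That the strata are left out of the model.** The text does not exclude them, and bladder management or setting may be among the variables kept.
- **That randomisation was unblocked, so imbalance within strata is to be expected.** The article calls the scheme simple and stratified and is silent on blocks.
- **That the survey covariates should leave the primary model.** The survey is described as pre hoc, so selection is not driven by trial outcomes. Removing variables judged prognostic would give up the same efficiency that including the strata is meant to gain.

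**Conclusion.** The point holds in a limited form. The design stratifies by two factors, and the stated covariate rule makes their place in the primary model depend on a survey rating. Their inclusion is not guaranteed.

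The consequence is conditional. Under the assumptions above, leaving out both factors costs about 0–1 points of power at stratum hazard ratios up to 1.5, 2–3 points at 2 (HR 0.640 against 0.627–0.628) and 8–9 points at 3 (HR 0.667 against 0.633–0.635). Including them when they are not prognostic costs essentially nothing. It would go too far to say that the reported hazard ratio will be attenuated or that power will be lost: the article gives neither stratum shares nor stratum effects, and the survey may have retained both factors. Confidence is high on the gap in the text and low on the size of any loss. The recommendation rests on the asymmetry: a possible gain at almost no cost.

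**What to change.** In Data analysis, state that the primary Cox model is stratified by, or adjusted for, bladder management type and inpatient/outpatient status whatever their survey rating. Choose one of the two forms in advance and give a prespecified rule for collapsing sparse cells. List the covariates that the survey retained; they may stay in the primary model alongside the strata.

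The cost is one or two sentences. Both factors had to be known at randomisation, so no new data are needed. The wording should be fixed before treatment allocation is revealed to the analysts.
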